### Outcome measurements

2.8

An overview of all questionnaires and outcome assessment markers can be found in Tables 3 and 4.

#### Brain health markers

2.8.1

##### Functional magnetic resonance imaging

2.8.1.1

The primary outcome will be evaluated at *T*_0_ and *T*_1_. Working memory function will be assessed using a digit 2-back task during fMRI. Prior studies have demonstrated differential blood BOLD responses in individuals with SCD compared to healthy controls during n-back task performance (117). This validated paradigm consists of three load conditions (0-, 1-, and 2-back), each presented in ten 30-s blocks, with a total task duration of 15 min. A continuous series of single-digit numbers will be shown and participants are instructed to identify whether the current digit matches the one presented (*n*) number of trials earlier. The task includes three working memory load conditions: 0-back (indicated by “–”), in which participants respond when a predefined target digit appears; 1-back (“<−”), in which they respond when the current digit matches the one presented immediately before; and 2-back (“<− −”), requiring detection of matches two positions back in the sequence. Primary outcomes of this study are hence (i) differential BOLD signal responses during the n-back working memory task and (ii) n-back task performance. Analysis of 1-back versus 0-back and 2-back versus 0-back contrasts will identify statistically significant brain activations at low and high cognitive loads, respectively. Main regions of interest include (bilateral) hippocampi, fusiform gyri and dorsolateral prefrontal cortices, based on their previous association with working memory (184, 185). Anatomical MRI scans (*T*_1_-weighted and FLAIR) will be used to assess total/regional grey matter and white matter integrity (hyperintensities via Fazekas scale or automated volumetry), focusing on the hippocampi and (pre)frontal- and temporal cortices as regions of interest.

##### Cognitive and mood assessments

2.8.1.2

Cognitive and mood outcomes will be assessed *T*_0_, *T*_mid_ and *T*_1_ visits (Table 3). The neuropsychological test battery (NTB) consists of the Cognitive-Functional Composite (CFC) and the Montreal Cognitive Assessment scale (MoCA) - the latter assessed at *T*_0_ only. The CFC battery provides a short and clinically relevant measurement of the cognitive domains that are sensitive to decline in early AD (186). The brief CFC NTB consists of six cognitive tests focusing on episodic memory, working memory and executive functions (186). Components included within the CFC are three components of the Alzheimer’s Disease Assessment Scale-Cognitive subscale (ADAS-Cog) (word recall, orientation, and word recognition), as well as a digit span test, verbal fluency test, and digit symbol substitution test. These tests can detect subtle worse performance in SCD subjects (112). The MoCA scale is a test with high sensitivity and specificity for minor cognitive defects (if scored ≤26/30) (187).

The Geriatric Depression Scale-15-item version (GDS-15) is a concise tool specifically developed to screen for depression in older populations, with established cut-offs and has demonstrated high sensitivity and specificity in older adults (188). The Generalized Anxiety Disorder-7 (GAD-7), a seven-item questionnaire, validated for use in older adults, will be employed to evaluate the presence of anxiety symptoms in daily life (189, 190). Subjective cognitive decline, will be measured via the Cognitive Failure Questionnaire (CFQ), a 25-item scale quantifying the frequency of everyday cognitive lapses (191, 192).

##### Brain health related blood markers

2.8.1.3

The *apolipoprotein E (ApoE) genotype* will be measured at *T*_0_ following DNA extraction from whole blood. ApoE genotyping is a well-established genetic risk factor for AD. Carriage of the ε4 allele is an AD risk factor, while the ε2 allele has a protective effect (193). Within the SCD + criteria framework, the presence of the ApoE ε4 allele increases risk for SCD progression to MCI or AD (113). ApoE genotype modulates lipid metabolism, with potential consequences for cognitive function, and will be evaluated alongside lipid profiles (194, 195). Plasma *Aβ1–42/Aβ1–40* ratio, *Neurofilament light chain* (NfL) and *glial fibrillary acidic protein* (GFAP), are emerging AD biomarkers in blood, and will be measured at *T*_0_ and *T*_1_ with single molecule array (SIMOA) analyses (196). The Aβ1–42/Aβ1–40 ratio as a biomarker is strongly correlated with Aβ deposition in the brain, and is predictive of cognitive decline along the AD continuum (197, 198). In SCD, lower plasma ratios were associated with steeper rate of decline on tests for attention, memory, and executive functioning (199). NfL is released into the blood and cerebrospinal fluid (CSF) after axonal injury and is indicative of neuroaxonal degeneration (200). Increased serum levels are associated with cognitive impairment as seen in MCI, and may serve as a prognostic biomarker of AD (200, 201). Similarly, GFAP, a marker of reactive astrogliosis, is increased in preclinical AD and may serve as sensitive biomarker for indicating CSF Aβ pathology (202).

*Serum cortisol* and *brain derived neurotrophic factor (BDNF)* levels will be determined by ELISA at *T*_0_ and *T*_1_. Reduced cortisol levels have been associated with worsened overall cognitive functioning, and with MCI, potentially due to HPA axis alterations and glucocorticoid-induced neurotoxicity (157). *BDNF* is a neurotrophin that regulates neuronal development and function (203). BDNF has neuroprotective properties, modulates synaptic efficacy at both glutamatergic and GABAergic synapses and plays a crucial role in synaptic plasticity, particularly in late-phase long-term potentiation (204, 205). Abnormal BDNF levels have been seen in AD (206).

Neurotransmitters and tryptophan-related metabolites will be measured in serum using ultra-high-performance liquid chromatography with electrospray ionization tandem mass spectrometry (UHPLC-ESI-MS/MS) at *T*_0_ and *T*_1_ (207). Tryptophan metabolites play a central role in MGBA modulation, with metabolites that are neurotoxic (quinolinic acid) and neuroprotective (kynurenic acid), while the kynurenine/tryptophan (KYN/TRP) ratio may serve as a peripheral biomarker of neuroinflammation (159, 160, 208, 209). Several of these metabolites can cross the BBB and modulate cognitive and behavioural processes (210) Furthermore, microbiota derived tryptophan indoles have been associated with improved cognitive outcomes (82, 211). Metabolites from the following pathways will be quantified: Kynurenine pathway; Tryptophan hydroxylation pathway; Microbiota-associated tryptophan metabolites, Tyrosine pathway; Phenylalanine metabolism; Branched chain and other amino acids; Histaminergic system; Microbial-derived methylamines.

#### Gut health markers

2.8.2

##### Faecal sample collection

2.8.2.1

Participants will collect faeces at home using a faecal collection paper (Faecesvanger, Tag Hemi VOF, The Netherlands) and a collection container with a collection scoop incorporated in the lid (Sarstedt, Nümbrecht, Germany). Participants will be instructed to collect from three different topographical locations of the faeces, and fill the container until two-thirds. Directly after collection, samples will be stored at −20 °C at home. Samples will be transported under frozen conditions in cooler bags with ice packs to the research facility and immediately stored at −80 °C upon arrival.

##### Gastrointestinal questionnaires

2.8.2.2

Gastrointestinal symptoms will be assessed using the Gastrointestinal Symptom Rating Scale (GSRS) and the Bristol Stool Scale (BSS). The GSRS includes 15 items across five symptom clusters: abdominal pain, reflux, indigestion, constipation, and diarrhoea, scored from 1 (no discomfort) to 7 (very severe discomfort) (212). It is validated for use in healthy adults and has been applied to assess changes in gastrointestinal symptoms with increased fibre consumption (213). The BSS is a seven-point scale that categorises stool form, with Types 1–2 indicating constipation, Types 6–7 diarrhoea, and Types 3–5 considered normal. It includes pictorial representations and is widely used in clinical and research contexts (214). The GSRS will be completed at all study visits and weekly during the first month. The BSS will be completed with each faecal sample collection.

##### Intestinal transit time

2.8.2.3

ITT is in an indicator of gut motility and function (215). In addition, ITT is significantly associated with gut microbiota richness and composition (216). Participants will be asked to consume two muffins, containing in total 1.5 gram blue colouring agent (EFSA approved for use in food: E133, E122). Time and date of consumption will be recorded, followed by time of first visualisation of blue/green colour in stool passage on the BSS questionnaire form. ITT can then be calculated (215).

##### Microbiota analysis

2.8.2.4

Quantification of the total number of bacteria via the total 16S rRNA copy number and quantifications of selected bacteria, such as the main phyla *Bacteroidetes* and *Firmicutes*, and *Bifidobacterium* and *Lactobacillus* species that are expected to change upon intervention, will be determined by droplet-digital PCR (ddPCR). Qualitative microbiota composition will be determined by 16S rRNA gene-based sequencing. Bioinformatic analysis will focus on changes in both richness, diversity and compositional changes. Analysis of the microbiota functional pathways will be carried out in R by Picrust, Tax4fun and KEGG pathway analysis to search for alterations in microbiota activity caused by the interventions (217, 218).

##### Microbiota derived metabolites

2.8.2.5

Short chain fatty acids (acetate, propionate, butyrate, valerate) as well as branched chain fatty acids (iso-valeric acid, iso-propionic acid) will be measured in plasma (LC–MS/MS; liquid chromatography tandem mass spectrometry) and faecal samples (GC-FID; gas chromatography-flame ionization detection) (219).

##### Intestinal function

2.8.2.6

Ageing impairs gut barrier function leading to increased permeability and systemic inflammation (38, 220). Biomarkers such as intestinal fatty-acid binding protein (iFABP) indicate epithelial damage, while LPS-binding protein (LBP) and soluble cluster of differentiations 14 (sCD14) reflect immune activation following LPS translocation (221). Zonulin regulates tight junctions (222), while elevated calprotectin and lipocalin indicate intestinal inflammation (223–226). Ageing is also associated with reduced mucosal thickness and soluble immunoglobulin A (sIgA) expression, compromising mucosal defenses (33, 35). Water content is a more reliable marker of stool consistency than questionnaire forms, while faecal pH indicates faecal SCFA levels (219). Faecal water content and pH (219), faecal intestinal inflammatory markers (Calprotectin, Lipocalin-2, *β*-defensin, sIgA), plasma/serum intestinal integrity markers (iFABP, LBP, sCD14) and tight junctional integrity (Zonulin) will be analysed by commercially available ELISAs.

#### Metabolic and inflammatory markers

2.8.3

Increased low-grade, systemic inflammation is seen with ageing (227) and may lead to neuroinflammation (228) and neurodegenerative processes (229). *Systemic inflammation* will be measured using an O-link cytokine panel (96 inflammatory markers) (230). Vitamin D insufficiency is common amongst older adults in Northern Europe and has been linked to inflammation, intestinal dysfunction, and cognitive decline (231, 232). *Serum vitamin D* will be assessed by the KCHL laboratory, ZGV. Insulin resistance is a known predictor of cognitive decline (158), while abnormal total cholesterol and HDL levels have been associated with increased risk of cognitive impairment (233, 234). *Metabolic markers* (fasting glucose, insulin, and HbA1c) as well as a *lipogram* (HDL, LDL, total cholesterol, triglycerides) will also be analysed at KCHL laboratory.

#### Dietary assessments

2.8.4

Dietary intake will be assessed by means of a food-frequency questionnaire (FFQ), which has been adapted for ease of calculation of a Mediterranean-DASH diet Intervention for Neurodegenerative Delay (MIND)-diet score (235). The MIND-NL score has been tailored to the Dutch context by incorporating commonly consumed Dutch food products, converting serving sizes to weights or volume amounts. The MIND diet dietary pattern has been designed as a preventative dietary pattern for cognitive decline, and higher adherence has been shown to be associated with protective effects on global cognition and lowered dementia risk (236). The FFQ will additionally be used to determine habitual dietary patterns and fibre intake.

#### Urine analysis

2.8.5

Urine will be collected at *T*_0_ and *T*_1_ for metabolomic analysis related to microbiota metabolites and neurotransmission.

#### E-health measures

2.8.6

Samsung Active 2.0 smartwatches will be used to measure heart rate, physical activity and mood. Physical activity is measured using both the pedometer (step count) and accelerometer data. The software has been modified in accordance with the protocol used in the DiaGame Study (Maxima Medical Center, Eindhoven and the Eindhoven University of Technology) (237). This software modification incorporates a push notification asking the participant to record their mood from five provided options (sad, stressed, neutral, happy, and angry) using the Experiencer application (238). Push notifications will be sent at random throughout the day, with a cooldown period set to every 3 h to ensure participant engagement. A previous study indicated that there is a meaningful congruency with longer depression and anxiety questionnaires (239). Step count is recorded continuously in an accumulative manner, with data points logged whenever new pedometer data becomes available. Accelerometer and heart rate data are captured when the user engages with the watch during self-reports. Data from the heart rate monitor will be used to determine the resting heart rate, as well as being used to infer the frequency, duration, and intensity of periods of increased physical activity/exercise. For each feature, the mean and variance across the 7 days will be calculated. To validate the mood data gathered by the smartwatches, data will be compared to validated depression and anxiety questionnaires. Once the device has been returned to WUR, the data will be extracted and all collected data will be securely uploaded through the Application Programming Interface (API) of GameBus platform which controls and processes them according to the General Data Protection Regulation (GDPR) and the Dutch Act on Implementation of the GDPR. The data will be stored on secure GameBus servers during the study and research analysis and will be removed after the analysis and termination of the study (240).

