4. Immune and metabolic parameters	Inflammatory cytokines; Fasting glucose and insulin; HbA1c	
	Lipogram	LDL, total cholesterol, triglycerides

Tertiary objectives	Tertiary outcome measures	
To evaluate the effect of 26 weeks of inulin, resistant dextrin and seaweed fibre supplementation compared to placebo (maltodextrin) in older adults with SCD+ on:		
1. Physiological parameters		
	Heart rate	Measured by Samsung Active 2.0 Smartwatches
	Physical activity	
	BMI	Height, weight
	Blood pressure	
2. Mood- as determined by		
(i) Wearable Samsung Active 2.0 Smartwatches	Sad, stressed, neutral, happy, or angry	3 hourly mood tracking via push notifications
(ii) Questionnaires	Self-reported depression and anxiety	GDS-15, GAD-7

Aβ, Amyloid-beta; ApoE, Apolipoprotein E; BCFAs, Branched-Chain Fatty Acids; BDNF, Brain-Derived Neurotrophic Factor; BMI, Body Mass Index; BOLD, Blood Oxygen Level Dependent; BSS, Bristol Stool Scale; CFC, Cognitive Functional Composite; ddPCR, Droplet Digital Polymerase Chain Reaction; FLAIR, Fluid-Attenuated Inversion Recovery; (f)MRI, (Functional) Magnetic Resonance Imaging; GAD-7, Generalised Anxiety Disorder-7; GDS-15, Geriatric Depression Scale (15-item); GFAP, Glial Fibrillary Acidic Protein; GSRS, Gastrointestinal Symptom Rating Scale; HbA1c, Glycated Haemoglobin A1c; iFABP, Intestinal Fatty Acid Binding Protein; LBP, Lipopolysaccharide-Binding Protein; LDL, Low-Density Lipoprotein; LPS, Lipopolysaccharide; NfL, Neurofilament light chain; NTB, Neuropsychological Test Battery; ROIs, Regions of Interest; sCD14, Soluble Cluster of Differentiation 14; SCFA, Short-Chain Fatty Acids; sIgA, Secretory Immunoglobulin A; SCD+, Subjective Cognitive Decline Plus.

Exploratory outcomes include amongst others, to determine the effects on gut hormones. Additionally, further baseline and background data will be collected from all participants, including demographic information (age, sex, education), risk factor profile (LIBRA short-form questionnaire), weight, height, and blood pressure. Detailed medical history, current medication use, dietary intake and supplement use will be recorded via structured questionnaires. Frailty will be assessed using a frailty questionnaire and grip strength measurements. For female participants, obstetric and gynaecological history will be gathered at baseline.

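### Heart rate is described as captured at mood self-reports at least 3 hours apart, which cannot support the planned exercise frequency and duration measures or, without a rest rule, a resting heart rate

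*Protocol article*

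**What the plan says.** Section 2.8.6 (E-health measures) of the protocol article describes two ways in which the watch collects data. For steps: "Step count is recorded continuously in an accumulative manner, with data points logged whenever new pedometer data becomes available". For the other two signals: "Accelerometer and heart rate data are captured when the user engages with the watch during self-reports". The self-reports are mood questions, and their timing is given as: "Push notifications will be sent at random throughout the day, with a cooldown period set to every 3 h to ensure participant engagement". Table 1 describes the same schedule as "3 hourly mood tracking via push notifications".

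The section measures physical activity with both the pedometer and the accelerometer. It uses the heart rate data for two things: a resting heart rate, and "used to infer the frequency, duration, and intensity of periods of increased physical activity/exercise". It then adds: "For each feature, the mean and variance across the 7 days will be calculated". The word 'feature' is not defined.

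Table 1 lists heart rate, physical activity and watch-recorded mood as tertiary outcomes. The mood options are "Sad, stressed, neutral, happy, or angry", with no numeric coding. Section 2.9.1 assigns linear mixed models to the secondary and tertiary outcomes in one general sentence.

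**The concern.** Frequency and duration describe the start and end of exercise periods. To measure them, the signal must be sampled more finely than a bout lasts. Readings taken at prompts 3 hours or more apart miss most bouts entirely, and a reading that does land in a bout says nothing about when it began or ended. A resting rate needs readings known to be taken at rest, and the section gives no rule that ties any capture to rest.

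A reading also depends on the participant responding. Someone who is exercising may not stop to answer, so missing readings could be related to the quantity being measured.

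At stake are the exercise and resting-rate measures derived from heart rate. Followed as written, the plan would produce numbers labelled exercise frequency and duration that the data cannot contain. The primary outcome and the sample size are not involved.

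**Working it through.** The plan gives no figure on this point, so there is none to reproduce. The check asks what the stated capture rule can deliver.

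**Inputs from the article**
- Minimum gap between prompts: 3 h (section 2.8.6).
- Wear period: about 7 days between the two visits (section 2.6.1.2; section 2.8.6 also refers to 7 days).

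**Assumptions (not in the article)**
- 14 to 16 waking hours a day.
- Every prompt answered at once.
- Mean gap between prompts of 3 to 6 h. Three hours is the best case, because prompts are random and the cooldown is a minimum.
- Each capture lasts 30 to 60 seconds.

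**1. Maximum number of readings.** Per day: whole number of (waking hours / 3), plus 1.
- 14 h: 4 + 1 = 5 a day; 5 × 7 = 35 over the week.
- 16 h: 5 + 1 = 6 a day; 6 × 7 = 42 over the week.

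**2. Chance that a bout contains any reading.** With prompts at least 3 h apart, a bout shorter than 3 h can contain at most one, so the chance is bout length / mean gap.

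| Bout | Mean gap 3 h | Mean gap 4 h | Mean gap 6 h |
|---|---|---|---|
| 20 min | 11.1% | 8.3% | 5.6% |
| 30 min | 16.7% | 12.5% | 8.3% |
| 60 min | 33.3% | 25.0% | 16.7% |

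For a participant with one 30-minute bout every day, the expected number of readings during exercise in the week is 7 × 0.083 = 0.6 to 7 × 0.167 = 1.2. At best, such data estimate very roughly the share of time spent exercising. They cannot separate that share into how many bouts there were and how long each lasted.

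**3. Share of the day observed.** Six captures of 30 to 60 seconds in 16 waking hours: 6 × 30 / 57,600 = 0.3% to 6 × 60 / 57,600 = 0.6%.

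**4. Mood, if 'feature' includes it.** Take two hypothetical sets of 42 answers, in the order sad, stressed, neutral, happy, angry: (10, 5, 15, 10, 2) and (5, 10, 12, 13, 2). The count differences are 5, −5, 3, −3 and 0. Assign the scores 1 to 5 to the categories in all 120 possible orders. The largest difference in mean score is (5×5 + 3×4 + 0×3 − 3×2 − 5×1) / 42 = 26/42 = 0.62, and the smallest is −0.62. Sixty codings give a positive difference and 60 a negative one. Without a justified coding, a mean of the raw categories has no fixed direction.

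**The case against.** **The article does not say that heart rate is captured only at self-reports.** That is true. It is an inference from the contrast with the continuous step count, and the watch settings may be described in cited sources that are not shown. The inference is reasonable, since no other heart rate capture is described. If continuous capture exists, the sentence is wrong as it stands, so a correction is needed either way.

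**A resting rate is not ruled out.** This stands in part. Accelerometer data are captured at the same self-report and steps are logged continuously, so still readings might be identified. The section states no such rule.

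**A reader might infer that heart rate, physical activity and watch mood would all be wrong.** The documents do not support this. Table 1 lists heart rate and physical activity in general terms, not exercise bouts. An average heart rate over prompted readings is a meaningful quantity if labelled as such. Step count is continuous and remains usable.

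**A reader might infer that a mean and variance of the mood categories are planned.** No sentence says so. The phrase about each feature follows the heart rate and activity sentences and may refer to those alone, or to derived mood features such as the share of each answer, for which a mean and variance are valid. How a tertiary item is scored is also commonly left to the full plan. What stands is that the section opens by naming mood among the watch measures and never limits the term, so the stated rule can be read to cover it.

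**Conclusion.** The stated capture rule and the exercise measures derived from heart rate do not fit together. With at most 5 to 6 readings a day, a 30-minute bout has about an 8% to 17% chance of being sampled at all, and its duration cannot be measured. Those figures rest on the assumed waking hours, prompt gaps and full response; missed prompts would lower them. The resting rate is unsupported as written but could be recovered in part with a rule for identifying rest. The conclusion also rests on reading the capture sentence as a full description of heart rate collection.

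The mood point is conditional: a mean, variance and linear mixed model would not be meaningful for the raw five categories, if that is what 'feature' covers. Only tertiary outcomes are affected, so this is a minor point that is cheap to correct.

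**What to change.** - Base the physical activity outcome on the continuous step count, for example daily steps.
- Drop the exercise frequency and duration measures derived from heart rate.
- Report heart rate as heart rate at self-report. Call it resting only for readings shown to be at rest from the concurrent accelerometer and step data, by a rule written down before analysis.
- If heart rate is in fact recorded continuously, correct the capture sentence instead; the derived measures can then be reconsidered.
- Define 'feature'. If it includes mood, summarise mood as proportions of answered prompts, and state a model suited to proportions.

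The cost is a wording change in the analysis plan. It uses data already being collected, adds no procedure for participants, and gives up only measures that the described data cannot provide.
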